# Study protocol: multicenter double-blind, randomized, placebo-controlled trial of rituximab for the treatment of childhood-onset early-stage uncomplicated frequently relapsing or steroid-dependent nephrotic syndrome (JSKDC10 trial)

**DOI:** 10.1186/s12882-019-1470-3

**Published:** 2019-08-02

**Keywords:** Frequently relapsing nephrotic syndrome, Steroid-sensitive nephrotic syndrome, Rituximab

## Abstract

**Background:**

Eighty percent of children with idiopathic nephrotic syndrome respond well to steroid therapy, but up to 50% of patients with steroid-sensitive nephrotic syndrome exhibit frequently relapsing (FRNS) or steroid-dependent nephrotic syndrome (SDNS). Several studies identified the chimeric anti-CD20 monoclonal antibody rituximab as an effective treatment for patients with complicated FRNS/SDNS. Recent studies suggested that rituximab could also be a first-line treatment for early-stage uncomplicated FRNS/SDNS, although further studies are required to confirm its efficacy and safety.

**Methods/design:**

We are conducting a multicenter, double-blind, randomized placebo controlled trial to investigate the efficacy and safety of rituximab for the treatment of childhood-onset early-stage uncomplicated FRNS/SDNS. Patients will be allocated to receive two 375 mg/m^2^ doses (maximum dose: 500 mg) of either rituximab or placebo. Investigators are permitted to request the disclosure of a subject’s allocation code if he or she exhibits treatment failure. Additionally, if placebo-treated subjects display early relapse (a sign of treatment failure), they have the option to receive rituximab in an unblinded phase. The primary endpoint is relapse-free survival during the observation period.

**Discussion:**

The results will provide important data on the use of rituximab for patients with uncomplicated FRNS/SDNS. In the future, rituximab treatment will enable most patients with uncomplicated FRNS/SDNS to discontinue or reduce steroid therapy without relapse, and it is possible that rituximab could represent an immunosuppressive therapy for these diseases.

**Trial registration:**

This trial was prospectively registered to the JMACCT Clinical Trials Registry on September 6, 2018 (Trial ID: JMA-IIA00380).

## Background

Nephrotic syndrome (NS) describes a clinical presentation of edema, proteinuria, hypoalbuminemia, and hyperlipidemia. NS affects 1 to 3 per 100,000 children less than 16 years of age [1]. In Japan, the estimated incidence of INS is 6.49 cases per 100,000 children annually [2]. Multiple pathogenic mechanisms that ultimately disrupt the glomerular filtration barrier have been identified.

The majority of children with idiopathic NS (80–90%) are steroid-sensitive, with their proteinuria normalizing within 4 weeks of daily oral corticosteroid administration [3]. Most steroid-sensitive patients (90%) have minimal-change NS, whereas most steroid-resistant patients (80.5–94.4%) have focal segmental glomerulosclerosis or mesangioproliferative glomerulonephritis. Approximately 30% of patients experience only one attack before a subsequent cure after the first course of therapy, 10–20% of patients have three or four steroid-responsive episodes before a permanent cure, and the remaining 30–50% of patients are frequent relapsers making them steroid-dependent.

The long-term prognosis for most children with steroid-sensitive nephrotic syndrome is complete resolution of their disease over time and maintenance of normal kidney function; therefore, limiting the long-term adverse effects of treatment is an important objective. Children with frequently relapsing NS (FRNS) or steroid-dependent NS (SDNS) require prolonged corticosteroid therapy, which is associated with significant adverse effects, including impaired linear growth, behavioral changes, obesity, Cushing’s syndrome, hypertension, ophthalmological disorders, impaired glucose tolerance, and reduced bone mineral density. Adverse effects may persist into adulthood in young people, who continue to relapse after puberty [4].

To reduce the risks of corticosteroid-related adverse effects, children with FRNS or SDNS (FRNS/SDNS) may require other agents. The Japanese Society for Pediatric Nephrology treatment guidelines for idiopathic NS in children recommend cyclosporine (3–6 mg/standard body weight [kg]/day for 2 years), cyclophosphamide (2–2.5 mg/standard body weight [kg]/day for 8–12 weeks), and mizoribine (high dose, 7–10 mg/standard body weight [kg]/day) as immunosuppressive drugs for FRNS. Given the toxicity of these agents, alternative treatment options must be investigated. Rituximab, a chimeric monoclonal anti-CD20 antibody, is increasingly being used as a steroid-sparing treatment option for children with idiopathic NS. The 2012 Kidney Disease: Improving Global Outcomes clinical practice guidelines on glomerulonephritis introduced rituximab as a treatment option for childhood-onset complicated FRNS/SDNS, and its efficacy and safety for these conditions have been established [5–7].

Rituximab was approved in Japan by the Ministry of Health, Labor, and Welfare for complicated FRNS/SDNS on August 29, 2014 based on the results of RCRNS-01 [5] and RCRNS-02. In these studies, some patients who can discontinue immunosuppressive agents before rituximab treatment may achieve long-term remission after rituximab treatment without any treatment. It is possible that rituximab could weaken disease activity and alter long-term prognosis in these patients [8]. It is likely that rituximab can be used as a first-line drug to treat cases of uncomplicated SDNS. Indeed, rituximab has been used as a first-line treatment for uncomplicated SDNS at many centers in European countries [9].

Only a few trials have assessed the use of rituximab in early-stage uncomplicated SDNS. Recently, an open-label, noninferiority, randomized controlled trial tested whether rituximab is noninferior to steroids in maintaining remission in childhood uncomplicated SDNS. The results from this trial indicated that rituximab allows the complete withdrawal of steroids in patients with childhood SDNS without adversely affecting clinical outcomes and that the drug has an acceptable short-term adverse event profile [10]. One clinical trial indicated that rituximab is more effective than tacrolimus over a 12-month period in maintaining disease remission and minimizing corticosteroid exposure [11]. Despite these results, additional data are needed to inform clinical practice. We believe that rituximab is likely to be a standard treatment for frequent relapse or steroid dependence, which prompted us to create this protocol. Currently, the use of rituximab in Japan for uncomplicated FRNS/SDNS patients requires approval from the Ministry of Health, Labor and Welfare. The proposed clinical trial seeks to establish evidence for the use of rituximab for first-line treatment of uncomplicated FRNS/SDNS patients.

## Methods/design

### Aims

In this trial, we aim to evaluate the efficacy and safety of two 375 mg/m^2^ doses of IDEC-C2B8 (rituximab: a monoclonal antibody directed against the CD20 differentiation antigen expressed on the surface of B-cells) given at weekly intervals in patients with childhood-onset early-stage uncomplicated FRNS/SRNS.

We also aim to verify the duration of relapse-free survival during the unblinded observation period, clarify the IDEC-C2B8 blood concentration and human anti-chimeric antibody (HACA) production and peripheral blood B cell numbers, and assess the relationship between recurrence and adverse events.

### Study design (Fig. 1)

We are conducting a multicenter, double-blind, randomized, placebo-controlled trial of IDEC-C2B8 for the treatment of childhood-onset early-stage uncomplicated FRNS/SRNS. In total, 40 patients (20 in each group) from 12 institutions in Japan will be enrolled in this study.

**Fig. 1 Fig1:**
[figure not shown]
Flow diagram of the clinical trial set-up. The trial is a multicenter, double-blind, randomized, placebo-controlled study. After obtaining informed consent, randomization will be conducted. If subjects in the placebo group wish to receive IDEC-C2B8 after the initial phase, they will receive the drug in an unblinded phase

However, if subjects in the placebo group develop treatment failure [1] and wish to receive IDEC-C2B8 after the randomized blinded phase, they will be eligible for treatment with the drug during the unblinded phase.

#### Clinical trial diagram (Figs. 2 and 3)

The clinical trial period for each patient will begin on the date consent is obtained and end on the date of completion of the observation period. However, subjects who desire to transition to the unblinded phase and receive IDEC-C2B8 after the initial blinded phase will remain in the study until the end date of the unblinded observation period. The day on which the first dose of the investigational drug is administered during the blinded period will be set as “Blinded Day1.” The day on which the first dose of investigational drug is administered during the unblinded period will be set as “Unblinded Day 1.”

**Fig. 2 Fig2:**
[figure not shown]
Dosage regimen (blinded period). Investigators will administer the first dose of the investigational drug within 14 days after the date of randomization (the date the first dose of the investigational drug is administered is set as Blinded Day 1). The investigational drug will be administered via two 375-mg/m^2^ doses (maximum dose: 500 mg) separated by 1 week (Blinded Days 1 and 8)

**Fig. 3 Fig3:**
[figure not shown]
Dosage regimen (unblinded period). Investigators will administer the first dose of IDEC-C2B8 within 14 days after the date of allocation (the date the first dose of IDEC-C2B8 is administered is set as Unblinded Day 1). IDEC-C2B8 will be administered via two 375-mg/m^2^ doses (maximum dose: 500 mg) separated by 1 week (Unblinded Days 1 and 8)

#### Definition of treatment failure

In this study, treatment failure is defined as follows:Treatment failure (1): Relapse occurring prior to Week 25 (Blinded Day 168).Treatment failure (2): Diagnosis of frequent relapse (two or more relapses)/steroid dependence between Weeks 25 (Blinded Day 169) and 53 (Blinded Day 365).Treatment failure (3): Diagnosis of steroid resistance after the blinded observation period.

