### Study patients

The inclusion criteria for patients are as follows:Fulfill the diagnostic criteria of idiopathic NS (the International Study of Kidney Disease in Children [ISKDC] idiopathic NS diagnostic criteria are used as a reference during the patient’s initial diagnosis).Younger than 18 years at the time of onset of idiopathic NS.Diagnosis of frequent relapse (two or more relapses within 6 months after initial remission or four or more relapses within any 12-month period) or steroid dependence (two consecutive relapses during steroid therapy dose reduction or within 2 weeks of discontinuation of steroid therapy), as well as confirmation of those dates of NS relapse prior to assignment.No history of treatment with any immunosuppressant for NS.Observation of steroid sensitivity during the treatment of relapse immediately prior to assignment.CD20-positive cell count of at least 5/μL in peripheral blood.Ability to stay in the hospital overnight on all days of planned investigational drug administration.Provision of consent by the patient (aged 20 years or older) or a legal representative (parents or legal guardians) using a document approved by the institutional review board after receiving an adequate explanation regarding the implementation of this clinical trial.

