### Outcomes

The primary endpoint is the time of relapse-free survival during the blinded observation period (days 1–365), assessed as the period from the date of assignment/allocation until that of the first relapse following the commencement of investigational drug administration. Secondary endpoints are the time to treatment failure, total steroid dosage, and changes in the number of B-cells in peripheral blood. Other endpoints are the time of relapse-free survival during the unblinded observation period (days 1–365), IDEC-C2B8 blood concentration, HACA production ratio, and adverse events. Adverse events will be recorded throughout the trial period and assessed using the Japan Clinical Oncology Group (JCOG) Japanese-language version (September 12, 2017) of the Common Terminology Criteria for Adverse Events version 4.0.

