### Statistical analysis

The objective of the primary analysis (the primary endpoint) in this clinical trial is to examine whether the IDEC-C2B8 group has significantly longer relapse-free survivals than the placebo group. The “relapse-free survival between the two groups will be equal” null hypothesis will be tested using the stratified log-rank test with the subject population receiving at least one dose of the investigational drug administration and measured the data for the assessment of primary endpoint (full analysis set). If the relapse-free survival is shorter in the IDEC-C2B8 group than in the placebo group, the test is one-sided because statistical significance is not important. One-sided significance level was set at 2.5%. If recurrence free survival is significantly longer in the IDEC-C2B8 group than in the placebo group, it can be concluded that IDEC-C2B8 is a useful treatment. Cumulative relapse curves and estimation of time to relapse will be performed using the Kaplan-Meier method and stratified log rank test of time to treatment failure.

The following analyses for the secondary and other endpoints are planned.

The total steroid dose in the blinded observation period will be analyzed using the analysis of covariance.

Median of the time to normalization of peripheral blood B-cells and its 95% confidence interval will be estimated using the Kaplan-Meier method.

The relationships of normalization of the number of peripheral blood B-cells with the presence or absence of relapse and with adverse events will be evaluated in each blinded observation period using Fisher’s exact test.

The proportion for the HACA production in each period with its 95% confidence interval will be estimated and the relationship of the presence or absence of HACA with adverse events will be evaluated in each period by Fisher’s exact test. IDEC-C2B8 blood concentration will be summarized to maximum blood concentration (C_max_), half-life period (T_1/2_), mean residence time (MRT) and area under the concentration-time curve (AUC), and the mean and standard deviation of these parameters will be calculated.

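### Treatment failure (3) counts steroid resistance only after Day 365, so resistance diagnosed in Days 169–365 after a single late relapse is never a treatment failure

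*Protocol article*

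**What the plan says.** The protocol article, Definition of treatment failure, lists three routes:

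- Failure (1): a relapse before Week 25, with Blinded Day 168 given as the limit.
- Failure (2): frequent relapse (at least two relapses) or steroid dependence, diagnosed from Blinded Day 169 to Blinded Day 365.
- Failure (3): "Diagnosis of steroid resistance after the blinded observation period".

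Outcomes fixes the period in question, since relapse-free survival is measured "during the blinded observation period (days 1–365". The only definition of steroid dependence is in the inclusion criteria (Study patients): "steroid dependence (two consecutive relapses during steroid therapy dose reduction or within 2 weeks of discontinuation of steroid therapy".

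The same term is used in three other places:

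- Outcomes: "Secondary endpoints are the time to treatment failure". Statistical analysis plans a "stratified log rank test of time to treatment failure".
- Prohibited combination therapy or concomitant medication: immunosuppressants are barred except in treatment failure.
- Conditions for urgent allocation code disclosure: treatment failure is one of three grounds for disclosure.

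On follow-up, the Clinical trial diagram section has each patient's trial period "end on the date of completion of the observation period". The exception is for "subjects who desire to transition to the unblinded phase", who stay until the unblinded observation period ends.

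**The concern.** The three routes should between them cover every unfavourable course that the trial means to call a failure. Steroid resistance is clearly meant to be one, since it has its own route. As printed, that route opens only once the blinded observation period has closed. Resistance that develops inside the period after a single late relapse is therefore left out, although it is arguably the worst outcome such a relapse can have.

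Read literally, the patient is not an event in time to treatment failure, does not fall under the exception to the immunosuppressant ban, and lacks the treatment-failure ground for code disclosure. Sites that read *after* differently could classify identical patients differently.

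**Working it through.** **Classification of a test patient.** Suppose the only relapse is on Day 200 and steroid resistance is diagnosed on Day 230.

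- Failure (1): no, because Day 200 is past Week 25.
- Failure (2): no. There is one relapse, not two, and steroid dependence by the definition in Study patients needs two consecutive relapses.
- Failure (3): no, because Day 230 is not after Day 365.

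Two neighbouring cases show where the gap ends. Relapse on Day 100 with resistance on Day 130 is failure (1). Relapse on Day 350 with resistance on Day 380 is failure (3) on paper. No other section of the article closes the gap. Failure (2) is also unlikely to catch the patient later, because a second relapse presupposes a remission.

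**What failure (3) can contribute as printed.** Patients who do not enter the unblinded phase leave the trial when the observation period ends, so failure (3) lies beyond their follow-up. The body text under Study design (Fig. 1) admits placebo patients to the unblinded phase only after failure (1), so these patients have already failed. The Fig. 1 caption and the Clinical trial diagram section word entry more loosely, by patient wish. On that reading failure (3) could be a first event, but only in placebo patients moved to open-label rituximab. Neither reading serves the randomised comparison.

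**Expected number exposed to the gap.**

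Inputs: 20 patients per group; 1-year relapse-free rates *p* of 0.66 (rituximab) and 0.01 (placebo), with exponential relapse times (Sample size). The planning hazards reproduce: −ln 0.66 = 0.416 and −ln 0.01 = 4.605, ratio 0.09, against the stated 0.42, 4.60 and 0.09.

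Assumption: resistance is diagnosed 28 days after relapse. Background describes steroid-sensitive children as those "with their proteinuria normalizing within 4 weeks of daily oral corticosteroid administration", which makes four weeks a natural window. A relapse must then start by Day 365 − 28 = Day 337 to be diagnosed by Day 365.

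Formula: S(d) = p^(d/365). First relapses in a window = 20 × (S at start − S at end).

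| | Rituximab, p = 0.66 | Placebo, p = 0.01 | Both |
|---|---|---|---|
| S(168) | 0.826 | 0.120 | |
| S(337) | 0.681 | 0.0142 | |
| S(365) | 0.66 | 0.01 | |
| Failure (1), to Day 168 | 3.48 | 17.60 | 21.08 |
| First relapse Days 169–337 | 2.89 | 2.12 | 5.01 |
| First relapse Days 338–365 | 0.43 | 0.085 | 0.51 |

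With the article's alternative rituximab rates of 0.50, 0.40 and 0.30, the Days 169–337 total becomes 6.11, 6.65 and 7.03.

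**Expected number misclassified.** The article gives no share of late relapses that prove resistant, so a range is shown:

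| Assumed resistant share | Of 5.01 | Of 7.03 |
|---|---|---|
| 1% | 0.05 | 0.07 |
| 5% | 0.25 | 0.35 |
| 20% | 1.00 | 1.41 |

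One misclassified patient needs a share of 1/5.01 = 20%, or 1/7.03 = 14% at the 0.30 rate.

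**The case against.** The strongest reply is that this is a wording slip in a condensed article. The surrounding text points to *during*: the immunosuppressant ban runs only to the end of the observation period, and follow-up stops there for most patients, so a failure route that opens afterwards would do almost no work. The full protocol, from which sites presumably operate, is not shown. This limits what can be inferred about conduct, but it does not correct the printed rule. Failures (1) and (2) are consecutive time windows, so a reader can naturally take (3) as the next one.

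The second reply is rarity. Study patients requires steroid sensitivity at the relapse just before assignment and excludes steroid-resistant disease, so a 20% resistant share is purely hypothetical. This stands and keeps the point minor.

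Third, excluding failure (2) carries an eligibility definition of steroid dependence into an outcome definition. That is fair, but it is the only definition the article gives. Even if the relapse before assignment were counted, a late relapse well after steroids had stopped would not qualify.

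Fourth, the consequences for care are uncertain. Two adverse-event grounds for code disclosure remain, and effects on treatment cannot be judged from the article. This also stands.

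Finally, a relapse in Days 338–365 whose resistance would be diagnosed after follow-up ends can be regarded as ordinary administrative censoring. How to handle it is a design choice and not part of the error.

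**Conclusion.** The concern holds, at minor severity. The three definitions, read with days 1–365 and with steroid dependence as two consecutive relapses, leave out a patient whose single relapse falls in Days 169–365 and is diagnosed steroid-resistant by Day 365. The gap itself rests on no numerical assumption.

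Its size does. Under the planning rates and a 28-day diagnosis, about 5 of 40 patients (7 at the least favourable rituximab rate) have a first relapse in the exposed window, and probably fewer than one would be misclassified. No direction of bias is established: the exposed first relapses divide 2.9 to 2.1 between rituximab and placebo, and the resistant share in each group is unknown. The primary endpoint counts every first relapse and is unaffected.

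**What to change.** Restate treatment failure (3) as: *steroid resistance diagnosed during the blinded observation period (Blinded Days 1–365)*. The test patient above then fails on Day 230. The sections on prohibited medication, code disclosure and outcomes use the shared term and need no further edit.

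If a steroid-resistance criterion is also wanted for the unblinded phase, define it separately and keep it out of the blinded time-to-treatment-failure analysis.

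Optionally, say whether a relapse that starts by Day 365 but is diagnosed resistant later counts. If it does, that patient's follow-up would have to run on to the diagnosis, up to about four weeks; about 0.5 first relapses are expected in Days 338–365.

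The cost is one to three lines of text. The sample size, significance level and primary analysis do not change.

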### Study patients

The inclusion criteria for patients are as follows:Fulfill the diagnostic criteria of idiopathic NS (the International Study of Kidney Disease in Children [ISKDC] idiopathic NS diagnostic criteria are used as a reference during the patient’s initial diagnosis).Younger than 18 years at the time of onset of idiopathic NS.Diagnosis of frequent relapse (two or more relapses within 6 months after initial remission or four or more relapses within any 12-month period) or steroid dependence (two consecutive relapses during steroid therapy dose reduction or within 2 weeks of discontinuation of steroid therapy), as well as confirmation of those dates of NS relapse prior to assignment.No history of treatment with any immunosuppressant for NS.Observation of steroid sensitivity during the treatment of relapse immediately prior to assignment.CD20-positive cell count of at least 5/μL in peripheral blood.Ability to stay in the hospital overnight on all days of planned investigational drug administration.Provision of consent by the patient (aged 20 years or older) or a legal representative (parents or legal guardians) using a document approved by the institutional review board after receiving an adequate explanation regarding the implementation of this clinical trial.

The exclusion criteria are as follows:Diagnosis of SRNS.Diagnosis of nephritic or secondary NS.History of severe infections such as pulmonary tuberculosis, deep mycosis, human immunodeficiency virus (HIV), hepatitis C virus (HCV), or hepatitis B virus (HBV) or other active viral infections.History of angina pectoris, cardiac failure, myocardial infarction, or serious arrhythmia.Receipt of a live vaccine within 4 weeks prior to assignment.Poorly controlled hypertension.Impaired renal function.Diagnosis of autoimmune diseases, IgA vasculitis, or systemic lupus nephritis.History of malignant tumors.History of organ transplantation (excluding corneal and hair transplants).Allergy to methylprednisolone, acetaminophen, or d-chlorpheniramine maleate.Any of the following abnormal clinical laboratory values at the time of registration: leukocytes, < 3000/μL; neutrophils, < 1500/μL; platelets, < 50,000/μL; severe liver dysfunction (if younger than 21 years: glutamic-oxaloacetic transaminase [GOT] or glutamic pyruvic transaminase [GPT] levels equal to or greater than 2.5× the upper limit of normal determined by the “Reference Intervals of Clinical Tests in Children Determined by a Latent Reference Value Extraction;” 21 years or older: GOT or GPT levels equal to or greater than 2.5× the upper limit of normal of each medical facility); hepatitis B surface (HBs) antigen, HBs antibody, hepatitis B core antibody, or HCV antibody positivity; HIV antibody positivity.Prior receipt of monoclonal antibodies of any type (mouse, rat, chimeric or human).Prior receipt of other investigational drugs within 6 month before assignment or participation in other studies at the time of assignment.Pregnancy, breastfeeding, or ability to become pregnant and refusal to use contraception during the study (confirmation by serum human chorionic gonadotropin test is required during screening).Assessed to be unfit for participation by the investigators.

